## The number of subjects to be enrolled, reason for choice of sample size, including reflections on (or calculation of) the power of the trial and clinical justification:

## We estimate a required sample size of at least 801 children to complete the 2-month study (89 per study arm and age group). To account for an estimated drop-out of 15-20%, a total of 990 evaluable children will be enrolled in each arm (110 per age group and study arm). Calculations and justification for sample size estimates are provided in Annex I.

## The level of significance to be used:

We are seeking to show (a) a reduction in number of subjects excreting vaccine poliovirus following a challenge vaccine dose (bOPV) among those vaccinated with bOPV or IPV compared to the control group; (b) an increase in secretory IgA following vaccination with bOPV or IPV compared to a control group; and (c) an increase in seroprevalence or antibody titers following vaccination with bOPV or IPV compared to a control group.

We use a level of significance of 0.05 (two-tailed test) and a power of 90% to detect the │20%│difference in proportion of subjects shedding vaccine poliovirus after the challenge dose of bOPV(see annex I).

## Criteria for termination of the trial:

The trial will be terminated if so directed by the Data and Safety Monitoring Board (DSMB) or other applicable agencies following safety concerns, or once sufficient numbers of study subjects have completed the study requirements.

## Procedures for accounting for missing, unused, and spurious data:

We will do "Modified Intention to Treat Analysis". All evaluable subjects will be included in the analysis. Evaluable subjects will mean the subjects who complete all study requirements including all study visits and provide sufficient quantities of sera samples for analysis. The subjects where sera are available, but missing a stool or gingival fluid sample, will also be included in the analysis.

## Procedures for reporting any deviation from the original statistical plan:

Additional analysis may be required, and will be conducted if agreed among the participating institutions.

## The selection of subjects to be included in the analysis (e.g., all randomized subjects, all doses subjects, all eligible subjects, evaluable subjects):

As stated above, only subjects who complete all study requirements including all study visits and provide sufficient quantities of sera samples for analysis will be included in the analysis.

# Direct Access to Source Data/Documents

The investigator/institutions will permit (by way of written agreement) trial-related monitoring, audits, IRB/IEC review, and regulatory inspection, providing direct access to source data/documents.

# Quality Control and Quality Assurance Procedures

### Study Monitoring and Source Data Verification

After appropriate ethical approval by an Institutional Review Board (IRB) is available (and the final protocol has been amended as required by IRB), the field study clinics will be set up to ensure the presence of all logistics. All study staff will be given detailed training on the study and their specific role. During the set-up of study sites and trainings, the requirements of GCP, protocol procedures, and all logistical issues will be discussed at length. The subjects cannot be enrolled until occurrence of these processes and their documentation.

After the study is initiated, the study monitor will be in regular contact with the sites to obtain information on the performance of the study. These contacts will be scheduled to take place at regular intervals. Subsequent to start of recruitment, routine monitoring visits would occur (approximately every 4 weeks) after prior appointment with the investigators.

The investigator and his/her staff are obliged to devote a suitable amount of time and an appropriate place for the monitoring visits. During each visit, the monitor will review the Case Report Form (CRF) of each subject in the study with regard to completeness, thoroughness and compliance with the protocol. In addition, at a minimum, the original subject data (e.g., entry cards, index cards, original findings) will be reviewed to ensure that:

- subject informed consent is incorporated;
- inclusion/exclusion criteria are properly followed;
- the CRF data are consistent with the questionnaires, the source data;
- all relevant clinical and laboratory findings and concomitant medication are documented in the CRFs;
- quantity and dosing schedule of concomitant medication is documented in the CRFs;
- quantity and dosing schedule of the Investigational/Comparator Product is in accordance with the protocol;
- all relevant information (e.g., any adverse event) has been recorded in the appropriate place in the CRFs;
- the Investigational/Comparator Product is being stored correctly, and its supply is being properly accounted for;
- Incorrect or illegible entries in the CRFs would be submitted to the investigator for correction.

The monitor will retrieve completed CRFs during the regularly held monitoring visits.

During the study trial period, the responsible Panacea Biotec staff will be available to answer questions with regard to the performance of the study.

### Auditing

In addition to the above outlined monitoring visits, the participating institutions may be audited. This audit may be carried out by representatives of Panacea Biotec or by the responsible regulatory authority(ies). Such an audit would be done to review whether the data has been properly recorded in the interim or final report and whether the performance of the study is in accordance with the protocol, the standard operating procedures (SOPs) developed for the study, and other relevant guidelines. Subject confidentiality will be maintained at all times.

Panacea Biotec Ltd. will immediately inform the investigators if an audit has been requested by a regulatory authority.

# Ethics

The study protocol will be reviewed and approved by the Ethical review committee (ERC) at WHO/HQ and by the Institutional Review Board of the Indian Council Medical Research. The study will be approved for implementation by the Drug Controller General (India).

# Data Handling and Record Keeping

The questionnaire data will be double-entered into an electronic data file; the laboratory data will be provided in electronic form and merged based on a common identifier. The original questionnaires will be stored with the Sponsor. Copies of all study documentation, including the questionnaires will be sent to WHO for long-term storage.

**Description of the roles and responsibilities of the institutions participating**

1. **WHO** will be a funding partner, and has an interest to ensure that the highest possible standards are applied, and that the trial will produce data that will be accepted not only in India, but by regulatory authorities elsewhere. In addition, contribution of WHO will include:
   - 1. Design the study and monitor implementation through visits to the study sites
     2. WHO will provide partial funding (as discussed during the licensing process). Funding would be made available through a technical services agreement to the study site(s) and the laboratory. Funding will include contracting healthcare workers involved in study procedures (physicians, vaccinators, laboratory technicians and others).
     3. SMOs from the National Polio Eradication Program (WHO) will enroll study patients, conduct data collection, supervise adherence to study protocols and standard operating procedures, and monitor processing, storage and transportation of specimens.
     4. Several laboratories from the WHO polio laboratory network in India will process blood and stool samples.
     5. WHO will receive the final clean data set (questionnaire + laboratory data) as soon as available and review report(s) and articles for publication.
2. **The Indian Council for Medical Research** will act as coordinator of the study in India, ensuring quality and safety of study procedures and data collection. The principal investigator, [name] works for the ICMR.
3. **CDC** will provide technical assistance in development of protocol and standard operating procedures, training, statistical analysis, and interpretation of results. CDC will also supervise training, implementation of study procedures and data collection. A CDC laboratory will process isolates from blood, crevicular and stool samples for additional tests measuring antibodies against poliovirus and for quality control of tests conducted in the Indian laboratories.
4. **Panacea Biotec Ltd** assumes roles and responsibilities of the sponsor of the study, including study insurance.
5. **The Ministry of Health and Family Welfare of India** will provide approvals for the study to be conducted and ensure the support of state health authorities.
6. The **Department of Health and Family Welfare of Uttar Pradesh** will facilitate the implementation of the study by allowing the use of public health care facilities as study sites. Health care workers in Public Hospitals or Public Health Care facilities may also need to see and counsel study patients who seek care after vaccine administration when study staff is not available.
7. **The International Vaccine Institute (IVI) Korea** will conduct the ELISPOT testing procedures.
8. **Imperial College, London will assist with high level statistical analysis.**

# Insurance

Panacea Biotec Ltd has umbrella insurance for clinical trials. This insurance will provide coverage for medical care in the event an adverse event occurs.

# Publication policy

All publications emanating from this trial will be reviewed by the participating institutions. Authors will be determined based on actual input into the publications, accordingto existing guidelines.

**Supplements**

Annex I - Sample size calculations

Annex II - Analytic plan

Annex III - Informed consent form

Annex IV - Subject information sheet and Assent Form

Annex V - Case Record Form (CRF)

Annex VI - Declaration of Helsinki

Annex VII - Serology protocol

Annex VIII – Antibody-capture ELISA for IgA and IgM to Polioviruses Type 1,2 and 3

Annex IX – Procedure for performing the one-step, dual color Enzyme Linked ImmunoSPOT assay (ELISPOT) for enumeration of Polio-specific IgG and Iga antibody secreting cells (ASC)

# ANNEX I

Sample size calculations

1. We are seeking to demonstrate that excretion of poliovirus following a challenge with bOPV is significantly lower in the bOPV or IPV vaccinated groups compared with the control group.

2. Definitions: (a) Significantly decreased defined as a decrease of ׀20%׀ in the proportion of study subjects vaccinated with IPV or bOPV who excrete virus following a challenge dose of bOPV compared with the proportion of control subjects who excrete virus after the challenge.

3. Applying a power of 0.90 (beta) and an alpha of 0.05, the following samples sizes would be required based upon assumed excretion of control and treatment (IPV or bOPV) groups:

| Control group excretion | bOPV or IPV excretion after challenge dose | | |
| --- | --- | --- | --- |
| 0.10 | 0.20 | 0.30 |
| 0.30 | 89 |  |  |
| 0.40 |  | 119 |  |
| 0.50 |  |  | 134 |

5. Using the most likely approach of low excretion in control and treatment groups due to previous exposure to OPV in all subject), we would require a sample of 89 for each study group, for a total of 801 subjects for the 3 study arms and 3 age groups per study arm.

6. With a sample size of at least 89 per study group, we should have a probability of 0.89 or more of estimating any of the differences in excretion of vaccine virus after the challenge dose within a ׀absolute value 20%׀

# 7. To account for drop-outs and ensure that sufficient subjects will complete all study requirements, we will enrol a total of 990 subjects, 110 per age-group (6-11 mo, 5-6 years and 10-11 years) and per study arm (IPV, OPV and controls).

# ANNEX II

Analytic plan

1. The primary endpoint of the study is reduction in excretion of poliovirus following a challenge dose of bOPV in subjects who have received a single dose of bOPV or IPV.

2. We will use chi-square test to compare the proportion of study subjects that excrete virus/or not following the challenge, in each study arm.

3. To use a conservative measure of p, we will apply a two-tailed test. We will also prepare 95% confidence intervals.

4. We will use non-parametric tests to compare the (median) amount of virus excreted after the challenge in each study arm.

5. We will also use non-parametric tests to measure and compare the distribution of antibody titers in serum (only for those with a positive titer; i.e., >1:8), among study groups and before and after treatment.

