# Trial Objectives and Purpose

## Mucosal immunity:

- To compare baseline mucosal immunity (through different methods) among three age groups with several degrees of protection acquired through immunization:
  - Infants 6-11 months of age will have received a few OPV doses
  - Children 5-6 years of age will have received multiple OPV doses in campaigns and are expected to have the highest levels of mucosal and humoral immunity
  - Children 10-11 years of age will not have received booster OPV doses for > 5 years. They are expected to have high antibody titers but may have waned mucosal immunity.
- To determine whether one dose of bOPV or IPV significantly reduces excretion of poliovirus types 1 and 3, respectively, following a challenge dose with bOPV, compared to an unvaccinated control arm.
- To determine whether one dose of bOPV or IPV significantly increases sIgA in crevicular fluids and stool samples, and to examine whether the increase in specific SIgA in these specimens is correlated to a reduction in excretion of Sabin poliovirus types 1 and 3 following the challenge with bOPV. This will allow evaluating the use of sIgA as a surrogate test for assessment of mucosal immunity.
- To determine the robustness of the mucosal immune response by study arm and age group, by measuring poliovirus antibody-secreting cells in an ELISPOT-spot assay 7 days after the administration of the study vaccine.

Humoral immunity:

- To determine whether one dose of bOPV or IPV will significantly increase seroprevalence and booster antibody titers compared to unvaccinated children.
- To assess whether one dose of IPV will significantly increase seroprevalence and antibody titers compared to a single dose of bOPV.
- To examine the correlations between antibody titers in blood and shedding of poliovirus after a challenge dose, for each vaccine study arm and age group.
- To examine the correlation between levels of IgA in serum and levels of secretory IgA in crevicular fluids and stool samples, before and after the booster vaccine dose, to gain further understanding on the mechanisms of mucosal immunity against poliovirus.
- To analyze correlations between levels of secretory IgA in crevicular fluids and stools and the ELISPOT test results, to better understand mucosal immunity against poliovirus.

Safety:

- To assess adverse events following vaccine administration.

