# Trial Design

Local community mobilization coordinators (CMCs) working with the Global Polio Eradication Initiative (GPEI) will identify families with children in the target age-group (i.e. 6-11 months, 5-6-years, and 10-11-years). Surveillance Medical Officers (SMOs) will visit households of potential candidate families, explain the study to the parents or guardians, and facilitate transportation to one of the study sites for those interested to participate. Approximately 10 study sites will be chosen in areas identified as high-risk for poliovirus transmission.

At the study site, a physician will conduct a short interview and physical examination. After obtaining informed consent from the parents (and assent from children of age 10-11 years), the study participant will be assigned a study number and allocated to a study arm. For this, the parent or child will select a closed envelope that includes the study arm from a basket. Then a baseline blood sample collected by venipuncture, oral (crevicular) fluid, and stool samples will be collected before vaccine administration.

Note: crevicular fluid will not be collected in the 6-11 month age group because of the absence of teeth.

In a subset of children 10-11 years of age (~175-200 children) a second blood sample will be collected at 7 days by venipuncture for the ELISPOT test.

In all children, at 28 days, another blood sample by venipuncture, another oral (crevicular) fluid sample and a stool sample will be collected before the subjects receives the challenge vaccine (bOPV). Thereafter, at days 3, 7 and 14 stool samples will be collected. And finally, at day 56, another serum sample and oral fluid sample will be collected. At this time, having fulfilled the study requirements, the children will exit the study.

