# Assessment of Efficacy

## Specification of the efficacy parameters:

Humoral immunity: Sera collected at study entry (day 0) and during the 7-, 28- and 56-day visits, will be examined for the presence (detectable) or absence of neutralizing antibodies to all three poliovirus serotypes. A reciprocal titer of 8 is considered to indicate the presence of neutralizing antibodies. In addition, a change from non-detectable (reciprocal <8) to detectable (reciprocal >8), or from below the highest dilution tested (reciprocal <1448) to the highest dilution tested (reciprocal >1448) will also indicate seroconversion. Although highest titre for neutralizing antibodies is 1024, we are taking end point dilution of half a log higher then 1024. This log of 10.5 is the highest observable titre and is being used because of high titres observed in this highly immunized population.

For participants with detectable antibodies, antibody boosting is defined as a >4-fold increase.

Mucosal immunity: Stool specimens will be collected at 0, 28, 31, 35 and 42 day visits. The samples will be examined for the presence or absence of polioviruses and other enteroviruses. In positive samples, the virus type will be determined following standard protocols from the World Health Organization (WHO) [20]. In addition, the amount (titration) of virus particles will be measured in those samples positive for poliovirus.

Semi-quantitative levels of sIgA in gingival fluid and stool samples will be determined using ELISA. High, medium and low levels will be determined and correlated in each study subject with serum antibody levels and with virus shedding after the challenge (Annex VIII-IX).

Additionally, in a subset of children 10-11 years of age, blood samples collected on days 0 and 7 will be tested to detect the amount of antibody-secreting lymphocytes specific for poliovirus using the ELISPOT technique.

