# Statistics

## A description of the statistical methods to be employed, including timing of any planned interim analysis:

A statistical analysis plan is provided in Annex II

**Humoral immunity**: Chi-square to compare the proportion of children seropositive in each study arm and age group; non-parametric tests to compare the titer distribution among the study arms.

**Mucosal immunity:** Chi-square to compare the proportion of subjects excreting poliovirus type 1, type 2, and type 3 at each collection point among study arms and age-groups; non-parametric tests to compare the median titers of poliovirus shed by individuals at each study arm and age-group.

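### The primary excretion test is a valid but unadjusted chi-square that leaves out the day-0 titre and stool sIgA the trial already collects, at some cost in power

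*Protocol*

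**What the plan says.** The Statistics section of the Protocol states "A statistical analysis plan is provided in Annex II". Item 2 of that annex gives the primary test: "We will use chi-square test to compare the proportion of study subjects that excrete virus/or not following the challenge, in each study arm". The Statistics section has a parallel sentence on the mucosal outcomes, which reads: "Chi-square to compare the proportion of subjects excreting poliovirus type 1, type 2, and type 3 at each collection point among study arms and age-groups". Neither place names a covariate or an adjusted model.

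The baseline data are planned for every child. Trial Design says: "Then a baseline blood sample collected by venipuncture, oral (crevicular) fluid, and stool samples will be collected before vaccine administration". Crevicular fluid is not taken in infants, but blood and stool are. Under Assessment of Efficacy, "Stool specimens will be collected at 0, 28, 31, 35 and 42 day visits". The day-0 samples yield neutralizing titres to each serotype, serum IgA, semi-quantitative stool sIgA (high, medium, low) and stool virus.

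These measures have other uses in the plan. One objective is "To examine the correlations between antibody titers in blood and shedding of poliovirus after a challenge dose, for each vaccine study arm and age group", and Assessment of Efficacy plans to correlate sIgA level with shedding. On error rates and power: "We use a level of significance of 0.05 (two-tailed test) and a power of 90" per cent.

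**The concern.** Annex I, item 5, explains the low excretion it expects by previous exposure to OPV. If prior immunity varies between children and predicts shedding after the challenge, an unadjusted test leaves that variation in the error term. It also leaves any chance imbalance in prior immunity between cells of about 89 uncorrected. Adjustment for baseline values would recover some precision from samples already being taken.

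This matters most where power is thin. Annex I requires 119 and 134 per group for two of its three scenarios but adopts 89. Because the protocol names Annex II as its statistical analysis plan, the unadjusted test is a stated choice and not a detail left open.

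**Working it through.** **Inputs.** From Annex I: control v vaccine excretion of 0.30 v 0.10, 0.40 v 0.20 and 0.50 v 0.30; required sizes 89, 119 and 134; 89 per cell adopted. Two-sided alpha 0.05 and power 90% (The level of significance to be used). Enrolment is 110 per cell with 15-20% drop-out. The strength of association between day-0 measures and shedding is not given and is varied below.

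**1. Annex I's sizes.** Uncorrected: n0 = [1.960·√(2p̄q̄) + 1.2816·√(p1q1 + p2q2)]² / d². Continuity-corrected: n = (n0/4)·[1 + √(1 + 4/(n0·d))]².

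For 0.30 v 0.10: n0 = (1.960×0.5657 + 1.2816×0.5477)²/0.04 ≈ 82, and the corrected n is 92. The corrected formula gives 92, 119 and 134 for the three scenarios. The last two match Annex I exactly. The 89 is reproduced at power 0.89, the figure in Annex I, item 6.

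**2. Power of the unadjusted test at 89 per cell.** z = [d·√n − 1.960·√(2p̄q̄)] / √(p1q1 + p2q2).

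- 30% v 10%: (1.887 − 1.109)/0.548 = 1.42, power 0.922
- 40% v 20%: (1.887 − 1.270)/0.632 = 0.97, power 0.835
- 50% v 30%: (1.887 − 1.358)/0.678 = 0.78, power 0.782

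With continuity correction these are 0.890, 0.790 and 0.734. At 94 per cell (110 × 0.85 = 93.5), uncorrected power is 0.935, 0.855 and 0.804.

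**3. Adjustment, by formula.** If the covariates correlate ρ with shedding, the variance is multiplied by (1 − ρ²). At ρ = 0.5 this acts like 89/0.75 = 118.7 per cell.

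| Assumed ρ | 30 v 10 | 40 v 20 | 50 v 30 | Gain, points |
|---|---|---|---|---|
| 0 | 0.922 | 0.835 | 0.782 | – |
| 0.2 | 0.932 | 0.850 | 0.799 | 1 to 2 |
| 0.3 | 0.944 | 0.868 | 0.820 | 2 to 4 |
| 0.4 | 0.959 | 0.894 | 0.849 | 4 to 7 |
| 0.5 | 0.975 | 0.925 | 0.887 | 5 to 11 |

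**4. Adjustment, by simulation.** 4000 runs, 89 per arm, one standardised baseline score, logistic likelihood-ratio test against chi-square, Monte Carlo standard error about 0.006. Entries are chi-square → adjusted.

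| Log-odds per SD | 30 v 10 | 40 v 20 | 50 v 30 |
|---|---|---|---|
| 0 (none) | 0.937 → 0.940 | 0.841 → 0.843 | 0.782 → 0.776 |
| 0.5 (weak) | 0.928 → 0.939 | 0.841 → 0.860 | 0.799 → 0.813 |
| 1.0 (moderate) | 0.926 → 0.954 | 0.826 → 0.893 | 0.792 → 0.852 |
| 1.5 (strong) | 0.929 → 0.979 | 0.842 → 0.932 | 0.796 → 0.901 |

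In the two underpowered scenarios the gain is about 1 to 2 points if weak, 6 to 7 if moderate and 9 to 10 if strong. It is smaller at 30% v 10%, where power is already high.

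**5. More realistic covariates.** A further simulation used three covariates: capped titre, three-level sIgA and rare day-0 excretion. Gains were about 0 to 5 points, there was no material loss when the covariates were uninformative, and null rejection was about 5-6%.

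**6. Pooled ages.** At 3 × 89 = 267 per arm, unadjusted power exceeds 0.99 in all three scenarios. The shortfall therefore concerns comparisons within an age group, which is how Annex I sizes the trial.

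**The case against.** The strongest reply is that a chi-square on randomised arms is a sound test, matches the absolute 20-point effect of Annex I, and holds its error rate despite chance imbalance. That stands. A reader might infer that the primary result would be biased or invalid; nothing in the documents supports this.

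A reader might also infer that the protocol expects titre to predict shedding. It does not say so: the objective poses the link as a question, and the sIgA objective concerns the increase after vaccination, not the day-0 level. The Preamble reports over 99% type 1 seropositivity in infants alongside continuing infection, and the 10-11-year group is expected to combine high titres with possibly waned mucosal immunity. With titres read only up to a ceiling and sIgA in three levels, the covariates may be weak. This also stands, and it is why no single gain can be quoted.

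Age is not simply ignored either. Annex II, item 2, omits it, but the Statistics section compares arms and age groups, and an analysis within age group needs no age term.

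Finally, day-0 excretion is background virus, not shedding after a known dose, and may be too rare to estimate. At 30% v 10% a pair of cells has only about 36 events (26.7 + 8.9). That argues against making it a mandatory covariate, but not against titre and sIgA.

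**Conclusion.** The point holds as an avoidable loss of efficiency in a valid test. The unadjusted power at 89 per cell (about 0.92, 0.84 and 0.78) follows from Annex I's own scenarios. The gain from adjustment rests on an assumed association: about 0 to 2 points if weak, 4 to 7 if moderate, about 10 if strong, none if absent.

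It is tempting to quote 5 to 11 points, but that range requires an assumed correlation of 0.5, the favourable end. It is also tempting to treat adjustment as the cure for adopting 89 where Annex I's table needs 119 or 134. It is not. At 50% v 30%, a correlation of 0.5 gives 0.887 by formula, and the simulation reaches 0.90 only with strong prediction. The sample-size shortfall is a separate matter. Adjustment is still worth making, because the data are already collected and the simulations show no material loss when the covariates carry no information.

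**What to change.** In Annex II, item 2, and in the mucosal-immunity paragraph of the Statistics section:

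- Make the primary between-arm analysis, within each age group, a logistic regression of excretion (by serotype) on arm, adjusted for log2 day-0 neutralizing titre of that serotype and day-0 stool sIgA category. Include age group wherever age groups are pooled.
- Use day-0 values only. Day-28 titre and sIgA may already reflect the study vaccine, and adjusting for them could remove part of its effect.
- Add day-0 excretion of that type only if it is common enough to estimate, under a rule fixed in advance.
- Report the standardised risk difference with its 95% CI, so that the 20-point effect stays the reported quantity. Keep the chi-square as supportive.
- State a rule for missing day-0 stool, for example a missing indicator, since the protocol keeps such children in the analysis. Titre raises less difficulty, because children who miss a scheduled blood sample are already excluded.

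The cost is plan wording and slightly more analysis work, with no new children or samples.
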